# Effect of Tai Chi combined with visual-action-sensory rehabilitation therapies on cognitive function in acute ischemic stroke: a study protocol for a randomized controlled trial

**DOI:** 10.1080/07853890.2025.2566877

**Published:** 2025-10-06

**Keywords:** Acute ischemic stroke, mirror neurons, action observation therapy, sensory observation therapy, cognitive rehabilitation

## Abstract

**Introduction:**

Early cognitive intervention in patients with acute ischemic stroke (AIS) is associated with better outcomes. ‘Visual-action-sensory’ rehabilitation therapies, including action observation therapy (AOT) and sensory observation therapy (SOT) have shown great potential in restoring cognitive function. A systematic review of some studies on the therapeutic effect of Tai Chi (TC)in stroke patients suggests potential benefits on depression, anxiety, and balance function. Therefore, combining AOT with TC may enhance brain functional connectivity and provide some cognitive improvements. Here, we describe a study protocol assessing the long-term effects of TC-AOT combined with SOT on cognitive function with AIS.

**Methods:**

This study is a dual-arm, single-center, single-blind, randomized controlled trial. A total of 86 AIS patients will be enrolled and randomly assigned in a 1:1 ratio to either the intervention group or the control group. The control group will receive conventional exercise education and follow-up. The intervention group first watched tactile stimulation followed by TC action videos, and then practiced imitating TC movements. The program will be implemented once a day for 30 min, 5 days a week for a duration of 8 weeks. Outcome measures will be assessed at baseline, week 8, and week 12. The primary outcome is global cognitive function and secondary outcomes are language, attention, executive function, memory, visuospatial ability, neuropsychological assessments, and quality of daily life.

**Conclusion:**

The study anticipates that the therapeutic program described here will help to reduce the incidence of cognitive impairment in AIS patients or delay its progression.

**Trial registration:**

We have registered at https://www.chictr.org.cn and the registration number is: ChiCTR2400088156.

## Administrative information

This paper is based on protocol version 2.0(2024-07-24). Trial sponsor: [name].

## Introduction

Stroke is the second leading cause of death and the third leading cause of disability worldwide [1]. Acute ischemic stroke (AIS), the most common type, accounted for 69.6%∼72.8% of cases in China [2,3]. At the acute stage, cognitive decline prevalence in ischemic stroke was 88.1%, and this impairment is linked to a higher risk of future disability [4]. To date, there are no proven effective treatments to reverse post-stroke cognitive impairment (PSCI) [5]. Therefore, it is crucial to initiate interventions at the preclinical and early stages to prevent and delay the onset of PSCI, as individuals at this stage still have the capacity to meaningfully engage in interventions [6]. At present, the non-pharmacological approach remains the main strategy to preserve cognitive functions in populations with cognitive decline [7]. Among these non-pharmacological interventions, action observation therapy (AOT) and sensory observation therapy (SOT) have shown great potential in restoring cognitive function.

AOT and SOT are key components of ‘visual-action-sensory’ rehabilitation therapy. In AOT, participants watch others performing goal-directed movements. This visual input activates motor-related brain regions responsible for planning and executing similar actions in the observer [8]. In SOT, participants observe others touching various textured materials. This process evokes internal simulation of the tactile experience, engaging somatosensory areas as if the participants themselves were feeling the stimuli [9]. The activation of these sensorimotor responses is mediated by the mirror neuron system (MNS). Mirror neurons are primarily located in the inferior parietal lobule, the ventral premotor cortex, and the caudal part of the inferior frontal gyrus [10]. These areas overlap with regions involved in cognitive functions. Through this widespread network, the MNS allows the brain to internally simulate observed actions or sensations, engaging corresponding functional areas as if the individual were performing the action or experiencing the stimulus. MNS is closely related to processes such as environmental information processing and sensory selection [11,12]. Thus, mirror neurons engage in complex cognitive processes by simulating observed content through visual input, facilitating the formation and strengthening of neural circuits. This can lead to the creation of new synaptic connections or the reinforcement of existing ones [13,14]. By forming new synapses, these therapies adjust and optimize learning and memory processes, thereby improving the efficiency of information processing and storage to compensate for cognitive impairments in stroke patients [15].

Previous systematic reviews have shown that AOT may benefit global cognitive function and language function in various populations [16,17]. However, we found that in most existing studies, participants were exposed to AOT videos that were fragmented and randomly presented, lacking systematic structure and continuity. To address this limitation, we adopted Tai Chi-based action observation therapy (TC-AOT), which uses videos of traditional Chinese Tai Chi routines characterized by spiralling motion and sequential coordination. Tai Chi movements are not only culturally familiar and widely accepted in China, but also support visuospatial processing, processing speed, and episodic memory [18]. Studies have shown that after TC-AOT intervention, there is a significant increase in brain functional connectivity between areas involved in executive attention and motor learning, including the temporal parietal junction (TPJ), supramarginal gyrus (SMG), inferior frontal gyrus (IFG), and insula [19]. The modulation of TPJ and SMG can influence motor attention in complex skilled actions [20,21], the IFG is crucial for controlling complex motor actions [22], and the insula integrates sensory information for motor planning [23]. Thus, TC-AOT holds significant potential benefits for cognitive rehabilitation.

SOT uses visual input to observe tactile sensory information in videos, enhancing patients’ information processing abilities, thereby promoting brain function recovery and cognitive improvement [9,24]. The mirror neuron system simulates sensory experiences; The mirror neuron system simulates sensory experiences; observing someone touch a material prompts the brain to recognize the action and partially simulates the tactile experience [9]. This understanding and prediction of others’ sensory states represent a highly complex cognitive function [25,26]. Therefore, it can be inferred that sensory observation activates sensory regions of the mirror neuron system, forming sensory representations that further enhance the brain’s sensory information processing and integration, potentially improving cognitive function.

Research has found that engaging in sensory observation before watching actions can more effectively improve cognitive function. This method’s effectiveness stems from deeply utilizing of the brain’s information-processing mechanisms [27]. Sensory observation, as an initial step, helps activate sensory processing areas in the brain, providing a strengthened neural foundation for subsequent action observation [28]. Once the brain is “primed” in sensory information processing, observing and simulating actions may be more profound and effective, promoting broader neural network activation and reorganization, further enhancing cognitive recovery and improvement. This finding highlights the importance of integrating sensory and action observation in cognitive intervention strategies.

Although some studies on the therapeutic effect of Tai Chi in stroke patients suggest potential benefits on depression, anxiety [29], and balance function [30], an evaluation of the cognitive benefits of Tai Chi in combination with other visual-motor-sensory’ rehabilitation therapies have received scanty attention. Therefore, this study combined TC-AOT with SOT to evaluate its cognitive effects on AIS patients. The results of this study will provide useful insights into the therapeutic value of combining AOT with Tai Chi to enhance brain functional connectivity and provide cognitive improvements.

## Patients and methods

### Study design and setting

This is a 2-group parallel, single-site, single-blind, hospital and home-based randomized controlled trial. Patients with AIS will be recruited from a Hospital in Zhejiang Province. The study consists of an 8-week intervention and a 4-week follow-up (Figure 1). All patients will provide written informed consent in accordance with the 2018 version of the Declaration of Helsinki.

**Figure 1. F0001:**
[figure not shown]
Flowchart of the trial design.

### Eligibility criteria

#### Inclusion criteria

The first stroke was in accordance with the Chinese guidelines for diagnosis and treatment of acute ischemic stroke 2023 [31] and was confirmed by brain CT or MRI.First onset of stroke, with disease duration of less than 14 days;The NIHSS score less than 5;Muscle strength of limbs > level 3.

#### Exclusion criteria

Patients currently participating in other cognitive interventions;Patients suspected of cognitive impairment before stroke (screening with AD8);Significant aphasia or severe cognitive impairment, inability to understand or cooperate with assessment and treatment instructions;Complicated with severe cardiopulmonary diseases, mental disorders, multiple organ failure, malignant tumors, or seizures.

### Sample size calculation

Calculate the sample size according to the following formula:

$$n=2{\left(\mu_{\alpha }+\mu_{\beta }\right)}^{2}\sigma^{2}/\delta^{2}$$
*n* is the sample size for each group; *μ_α_* is the u value corresponding to the Type I error probability, and *μ_β_* is the u value corresponding to the Type II error probability; *δ* donates the expected effect size, i.e. the absolute value of the difference in means between the two groups, and σ^2^ is the population variance, estimated by the sample variance, which is the mean of the variances of the two groups. *α* is set at 0.05 and *β* is set at 0.10. According to Yeh et al.’s study [32], σ = 4.985, δ = 2.33, the calculated sample size for each group is 30. Considering a 25% dropout rate in previous studies [33] and the potential for a higher dropout rate in cognition-related studies [34], we increased the dropout rate to 30%. Ultimately, we determined that each group should include 43 patients.

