### Data analysis

A statistician will analyse the data using SPSS 26.0 software, considering a P-value < 0.05 as statistically significant. Continuous variables will be presented as mean ± standard deviation or median with interquartile range, while categorical variables will be expressed as frequency and percentage. The outcome measures in this study are all continuous variables. Differences in outcomes at baseline, week 8, and week 12 will be analysed using repeated measures ANOVA or mixed linear regression analysis. Both the intention-to-treat (ITT) and per-protocol (PP) populations will be included in the analysis. The ITT and PP analysis results will be compared to ensure consistency. In cases of missing data, the last observed value will be carried forward for interpolation. A safety analysis will be performed to assess safety outcomes.

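### The printed formula and inputs give 97 patients per group, not 30; on those inputs 30 evaluable per group gives about 43% power, not 90%.

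*Protocol article*

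**What the plan says.** The Sample size calculation section gives n = 2(u_alpha + u_beta)²σ²/δ². It states that n "is the sample size for each group", that δ is "the absolute value of the difference in means between the two groups", and that σ² is the population variance, estimated by the mean of the two groups' variances. Alpha is 0.05 and beta is 0.10. The inputs come from one cited earlier study, and the result reads "σ = 4.985, δ = 2.33, the calculated sample size for each group is 30". Dropout of 30% is then allowed for: "Ultimately, we determined that each group should include 43 patients". The Methods paragraph of the abstract carries this forward: "A total of 86 AIS patients will be enrolled", allocated 1:1.

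The section does not say whether the test is one-sided or two-sided. The Data analysis section says only "considering a P-value < 0.05 as statistically significant". The sample size section mentions no baseline adjustment or repeated-measures gain. It also does not name the outcome to which σ and δ belong; the MoCA is the only primary outcome listed, so this note takes them to be MoCA points.

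**The concern.** The formula, its inputs and its result all stand in one paragraph, and the result does not follow from the rest. A standardised difference of 2.33/4.985 = 0.467 is moderate, and 30 per group is far too few to detect it with 90% power.

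This is the document's only justification for enrolling 86 patients. If the printed inputs are right, the trial is much less likely to detect its own target difference than the plan implies. A non-significant primary result could then be taken as evidence against the intervention when the trial was too small to say so.

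**Working it through.** **Inputs** (all from Sample size calculation): α = 0.05, β = 0.10, σ = 4.985, δ = 2.33, n per group, dropout 30%. Two-sidedness is an assumption; the one-sided result is shown beside it.

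**The plan's formula with the plan's inputs, two-sided**

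- (1.95996 + 1.28155)² = 10.507
- σ² = 4.985² = 24.850; δ² = 2.33² = 5.429
- n = 2 × 10.507 × 24.850 / 5.429 = 96.2, so **97 per group**
- With 30% dropout: 97/0.7 = 138.6, so **139 per group**, 278 in total

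The stated 30 is not reproduced; the formula gives about 3.2 times as many (96.2/30). The dropout step does reproduce: 30/0.7 = 42.9, so 43. The discrepancy therefore lies before the dropout step and carries through to 86.

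**Can another reading give 30?**

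| Reading | Two-sided | One-sided |
|---|---|---|
| As printed, 90% power | 96.2 | 78.4 |
| 80% power instead of 90% | 71.9 | 56.6 |
| Factor 2 omitted, 90% power | 48.1 | 39.2 |
| 4.985 taken as the variance, 90% power | 19.3 | 15.7 |
| Neither σ nor δ squared, 90% power | 45.0 | 36.6 |

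The one combination found near 30 omits the factor 2 and also uses one-sided alpha and 80% power. It gives 28.3, so 29, and contradicts both the printed formula and the printed beta. No reading tried that keeps the formula and beta comes near 30.

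**What would make 30 correct (two-sided, 90% power)**

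- σ = 2.33 × √(30/2) / 3.2415 = 2.78 with δ = 2.33, or
- δ = 4.985 × √(2/30) × 3.2415 = 4.17 with σ = 4.985

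**Power with the printed σ and δ (t-test, no adjustment)**

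| Evaluable per group | Two-sided | One-sided | Difference detectable with 90% power, two-sided |
|---|---|---|---|
| 30 | 42.9% | 55.7% | about 4.2 points |
| 43 | 57.2% | 69.3% | about 3.5 points |

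The normal approximation gives 44.0% and 58.2% for the two-sided column.

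**Power if the analysis adjusts for baseline**

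With correlation ρ between baseline and week-8 scores, the variance shrinks by the factor 1 − ρ². The document gives no ρ, so a range is assumed (two-sided t-test).

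| ρ | 30 per group | 43 per group |
|---|---|---|
| 0.5 | 54% | 70% |
| 0.7 | 70% | 85% |
| 0.8 | 84% | 95% |

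For 30 per group to suffice, 96.19 × (1 − ρ²) = 30, so ρ = √(1 − 30/96.19) = 0.83.

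**The case against.** **The error may be in an input.** If σ were really about 2.78, or δ about 4.17, then 30 would be right and the power would be 90%. This stands. The cited study is not available here, and the document cannot settle which number is wrong. The power figures above are therefore conditional on the printed inputs. The contradiction between inputs and result is not conditional.

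**43% is the pessimistic end.** The Data analysis section includes an intention-to-treat analysis with the last value carried forward, so up to 43 per group could be analysed, which gives 57%. It plans repeated measures ANOVA or mixed linear regression rather than a single t-test, and this may add power, as the range of correlations shows. These points stand, with limits. Carrying baseline values forward for dropouts may dilute the effect, so 57% is not assured. A group-by-time comparison of change gains less than baseline adjustment: change has variance 2(1 − ρ)σ², and with 30 per group the power is about 43%, 63% and 80% at ρ = 0.5, 0.7 and 0.8. The sample size section itself uses none of these gains.

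**Sidedness is not stated.** This is true, but a one-sided test still needs 79 per group and has about 56% power with 30, so the conclusion does not depend on it.

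**A null result might not be misread.** The document says nothing on how one would be interpreted, so this is a risk and not a stated plan. The arithmetic does not depend on it.

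**Conclusion.** The concern holds. The printed formula and inputs give 97 per group two-sided, or 79 one-sided, and not 30. Nothing elsewhere in the article corrects this.

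If σ = 4.985 and δ = 2.33 are right, unadjusted two-sided power for 2.33 points is about 43% with 30 evaluable per group and about 57% with 43. At correlations of 0.5 to 0.8, baseline adjustment raises these to 54–84% and 70–95%. As the section is written, 90% power with 30 per group has no support. The point must be fixed because it concerns the only stated basis for the trial's size.

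**What to change.** Correct the Sample size calculation section:

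1. Check σ and δ against the cited study. If either is misprinted, correct it and show that the formula then returns the stated number.
2. If both stand, state that the formula gives 97 per group, or 139 with 30% dropout, and say that the test is two-sided (or give the one-sided figures if that is what was meant).
3. If 86 patients is what is feasible, keep it, but replace the 90% claim with the delivered power: about 43% unadjusted for 2.33 points with 30 evaluable per group, about 57% with 43, and 90% only for differences of about 4.2 and 3.5 points respectively.

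Two additions would help, though the correction does not depend on them. One is the power under a baseline-adjusted analysis with an explicit assumed correlation. The other is a statement that a non-significant primary result will be reported with its confidence interval and not as absence of effect.

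The cost is one rewritten paragraph and a less favourable stated power. Correcting the statement needs no extra patients.

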### Recruitment

Potential participants in the hospital will be identified by screening the electronic medical records in the neurology ward to find patients who experienced their first ischemic stroke within 14 days of onset. A research coordinator will then contact these potential participants to assess their eligibility, ability to complete the questionnaire, interest in participation, experience using WeChat, and willingness to sign the consent form along with one of their family members.

### Randomization and blinding

The statistician will use SPSS 26.0 software to randomize the sequence numbered 1–86 using a random number generator. Random numbers for grouping will be generated and divided into two groups in a 1:1 ratio using visual binning. The grouping results are placed in opaque envelopes. Eligible participants will receive an envelope in registration order and hand it over to the intervention implementer. The researcher who sealed the envelopes will not be involved in participant inclusion, treatment, or assessment. Due to the nature of action-sensory observation, blinding participants and intervention implementers is not possible. However, participants will receive individual treatment, and the intervention implementers will not participate in outcome assessments. Evaluators and statisticians will remain unaware of group assignments.

### Interventions

In this prospective, two-arm, single-centre, randomized controlled trial study, we will recruit 86 acute ischemic stroke patients within 14 days of onset. Participants will be randomly assigned to either an intervention group (receiving TC-AOT combined with SOT) or a control group (undergoing routine cognitive rehabilitation) in a 1:1 ratio. All patients will receive routine treatment and conventional exercise education, delivered by professional therapists during hospitalization. After discharge, education and follow-up will be conducted by our medical and nursing team. Additionally, in the intervention group, patients will begin by watching a sensory activation video, followed by watching a video on 8 Trigram 5 Steps TC, and then engaging in TC exercises. The program will be implemented once a day for 30 min, 5 days a week, and will last for 8 weeks. Based on the results of the preliminary literature review and evidence-based analysis, and after an expert panel meeting, the interventions were ultimately developed as illustrated in Figure 2.

**Figure 2. F0002:**
[figure not shown]
TC-AOT combined with SOT therapy flow chat.

The AOT video selects the 8 Trigram 5 Steps TC released by the General Administration of Sports of China, and the sensory observation video was recorded by the researchers ourselves. The sensory observation for both the upper and lower limbs involved quick tapping with a wooden board (20s), brushing with silk (20s), and brushing with a cotton swab (20s).

In the hospital, the training will be conducted in the neurology ward. The intervention schedule will run from Monday to Friday, with one session in the morning (10:30–11:00) and three sessions in the afternoon (15:00–15:30, 15:45–16:15, and 16:30–17:00). Patients will be required to participate in only one session per day. After discharge, the researchers will send the videos to the patients and provide daily reminders from Monday to Friday to watch and imitate the videos. During the home-based intervention, a caregiver will accompany the patient throughout the entire video-guided training session and take three photos capturing the patient actively engaged in the intervention. These photos will be uploaded *via* the “Jielong Butler” WeChat applet as evidence of participation. Participants are required to complete this check-in five times per week. The total duration of the intervention will be 8 weeks.

### Outcomes

At baseline, patients will undergo the AD8 test to screen for pre-stroke cognitive impairment; those identified with such impairment will be excluded. Routine sociodemographic data will also be collected, including age, gender, marital/cohabitation status, employment status, as well as personal and family medical history, and smoking and alcohol consumption habits.

Validated assessment tools will be employed to evaluate global cognitive function, memory, language function, executive function, attention, visuospatial ability, activities of daily living, neuropsychiatric symptoms, and psychological status. Each scale will be analysed independently, no composite total score will be calculated across different scales.

Subjects will be evaluated at three time points: before the intervention (1–2 days before the start, T1), after the intervention (1–2 days following the 8-week intervention, T2), and during follow-up (4 weeks after the 8-week intervention, T3). The safety outcome, particularly the incidence of falls, will be monitored throughout the study.

### Primary outcomes

Montreal Cognitive Assessment (MoCA) [35] assesses visuospatial and executive function, naming, memory, attention and computation, language, abstract thinking, delayed recall, and orientation. The test comprises 30 questions and the highest possible score is 30. The sensitivity of MoCA is 92.4%, the specificity is 88.4%, the best abnormal cut-off point is: illiterate group ≤ 13 points, primary school group ≤ 19 points, junior high school, and above group ≤ 24 points.

